#### Psychological factors during pregnancy

Factors such as readiness to change behaviour [35], anxiety [36], depression [37,38] and body image [39,40] will be assessed at baseline and at 36 weeks gestation.

##### Readiness to Change Questionnaire

This researcher designed measure modifies an existing scale [35] to the weight loss context. There are 12 items which are rated on a five point scale from Strongly agree to Strongly disagree. The items refer to an individual's *readiness, importance *and *confidence *in adopting healthy lifestyle changes during pregnancy, including subjective ratings of the healthiness of current eating and physical activity behaviours.

##### Anxiety

Anxiety will be measured using the short version of the Speilberger State-Trait Anxiety Inventory (State). Responses to six statements include 'Not at all', 'Somewhat', 'Moderately' and 'Very much' (alpha0.82)[36].

##### Depression

Depression will be measured using the Edinburgh Postnatal Depression Scale, which has been validated to use in pregnancy [37]. Women will be classified as probably clinically depressed using a cut-off score of ≥ 13, providing a sensitivity of 100% and specificity between 87 and 95.7% [38].

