### Power, sample size and retention

A difference between groups of 20% is deemed clinically significant. The proportion of obese women gaining weight in excess of evidence based guidelines is approximately 65% [23]. It is estimated that 107 women per study arm (total of 214 participants) is required in order to detect a difference of 20% between groups with 80% power at a 0.05 level of significance [41]. Based on current booking numbers and the prevalence of obesity at the recruitment sites, approximately 74 women will be eligible to participate each month. To accommodate an anticipated 77% participation rate [42] and a 15% attrition rate [42], the required sample will be recruited in four and a half months.

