### Analyses

Analyses will be undertaken using STATA [43] and comparability of baseline characteristics will be assessed for participants in both groups. The intervention group will be compared to the control group by intention to treat analysis. Proportions of women restricting weight gain to recommended levels will be compared using chi-square tests and odds ratios. Comparison of means will be undertaken for continuous variables using t-tests where data are normally distributed, otherwise medians will be compared using Mann-Whitney U tests. Ranked or Likert scales will be analysed using cumulative odds ratios and 95% confidence intervals will be reported. Where differences in baseline characteristics exist that may be associated with outcomes, additional multivariate analysis will be performed.

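### The only handling of the EPDS that the protocol names is a cut at 13 or more; it should say that the 36-week total score is compared between arms

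*Protocol article*

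**What the plan says.** The Depression section of the protocol article names the instrument, "Depression will be measured using the Edinburgh Postnatal Depression Scale, which has been validated to use in pregnancy", and then one way of using it: "Women will be classified as probably clinically depressed using a cut-off score of ≥ 13". It supports the threshold with cited accuracy figures, "providing a sensitivity of 100% and specificity between 87 and 95.7" per cent.

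Under Psychological factors during pregnancy, depression is among the factors that "will be assessed at baseline and at 36 weeks gestation". The full score is therefore collected twice.

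None of the other psychological scales (readiness to change, anxiety, the two body attitude subscales, the figure rating scale) is given a cut-off.

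The Analyses section assigns chi-square tests and odds ratios to the weight-gain proportions and cumulative odds ratios to ranked or Likert scales. For other scales it says: "Comparison of means will be undertaken for continuous variables using t-tests where data are normally distributed, otherwise medians will be compared using Mann-Whitney U tests". None of these statements names the EPDS.

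**The concern.** Depression is the only psychological measure for which the article describes a yes/no class, and it describes nothing else for it. A reader would naturally take the depression outcome to be the proportion of women at or above 13.

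The secondary aim is to measure the effect of the care model on psychological factors, in women recruited on BMI and not on mood. A comparison at the cut ignores every change that does not cross 13. The sample size was set for a 20-point difference in a common outcome (weight gain above guidelines, about 65%). That gives no assurance for a less common binary outcome.

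At stake is whether a moderate shift in mood would be seen. The data needed to see it are already collected.

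**Working it through.** **Inputs from the article.** Sample size: "107 women per study arm (total of 214 participants) is required in order to detect a difference of 20% between groups with 80% power"; the significance level is 0.05. Reference rate for the primary outcome: "The proportion of obese women gaining weight in excess of evidence based guidelines is approximately 65" per cent. Attrition: "a 15% attrition rate". No EPDS positive rate, standard deviation, target difference or power is given for depression.

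**Assumptions.** Two-sided 0.05 (sidedness is not stated), normally distributed scores, a common shift of 0.4 SD between arms, and 5% to 25% of women scoring 13 or more.

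**1. The plan's own figure.** For 65% against 45%, the mean proportion is 0.55:

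n = [1.96 × √(2 × 0.55 × 0.45) + 0.8416 × √(0.65 × 0.35 + 0.45 × 0.55)]² / 0.20² = 96 per arm.

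With the continuity correction this becomes (95.94/4) × [1 + √(1 + 4/(95.94 × 0.20))]² = 106. The stated 107 agrees closely. It concerns weight gain and says nothing about depression.

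**2. Number analysed.** Expected recruitment is 74 × 0.77 × 4.5 = 256, and 256 × 0.85 = 218. So 214 is probably the number left after attrition, and 107 per arm is used as the main case. Because the Participants section calls 214 the participants, about 90 per arm (107 × 0.85 = 91) is shown as a second case.

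**3. Information kept by the cut.** For a normal score with a proportion p above the cut, the efficiency of the yes/no comparison relative to the score is φ(z)² / [p(1 − p)], where z is the cut in SD units.

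| p | z | φ(z) | p(1 − p) | Efficiency |
|---|---|---|---|---|
| 5% | 1.645 | 0.1031 | 0.0475 | 22% |
| 10% | 1.282 | 0.1755 | 0.0900 | 34% |
| 15% | 1.036 | 0.2332 | 0.1275 | 43% |
| 20% | 0.842 | 0.2800 | 0.1600 | 49% |
| 25% | 0.674 | 0.3178 | 0.1875 | 54% |

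The efficiency passes one half at about p = 21%.

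**4. Power for a 0.4 SD shift.** On the score, power = Φ(0.4 × √(n/2) − 1.96). With n = 107 this is Φ(2.926 − 1.96) = Φ(0.966) = 83%. With n = 90 it is Φ(2.683 − 1.96) = 77%.

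On the cut, a control rate p₁ becomes p₂ = 1 − Φ(z + 0.4), and the two proportions are compared.

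| Controls at 13 or more | After the shift | Power, cut, 107 per arm | Power, cut, 90 per arm |
|---|---|---|---|
| 10% | 4.6% | 33% | 28% |
| 15% | 7.5% | 41% | 35% |
| 20% | 10.7% | 47% | 41% |
| 25% | 14.1% | 52% | 45% |
| *Score, for comparison* | | *83%* | *77%* |

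The gap between cut and score is large across the whole range and under either reading of the sample size.

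**The case against.** The strongest reply is that the article never says the score is dropped. The Depression section says how women are classified. It does not say that the classification is the only analysis, or that the arms will be compared on it. The chi-square sentence in Analyses names only weight gain, and the tests for continuous variables could cover an EPDS total. A journal article condenses the full protocol, and a fuller analysis plan may settle the matter. All of this stands. A reader might infer that depression is reduced to a yes/no outcome, but the text supports only the weaker statement that the cut is the one handling named. What remains is that a reader applying the article as written has a class for depression and no sentence saying the score is compared.

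A reader might also conclude that most of the information is lost. That holds only if fewer than about 21% of women score positive, and the article gives no rate. Much is the safer word. Normality and an even shift are likewise assumptions. An effect confined to women near the threshold would narrow the gap.

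A third inference is that the quoted accuracy contradicts calling women above the cut probable cases. It does not. With 100% sensitivity, a positive woman is more likely than not a true case once prevalence exceeds (1 − specificity)/(2 − specificity). That is 0.13/1.13 = 11.5% at 87% specificity and 0.043/1.043 = 4.1% at 95.7%. The article gives no prevalence, so its figures do not refute the label.

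**Conclusion.** The point holds as a minor one on a secondary outcome. It is a useful clarification and not a contradiction in the article. The cut at 13 or more is the only EPDS handling stated, and comparing the arms on it would give up much of the score's information. The cut keeps about 22% to 54% of the efficiency at positive rates of 5% to 25%. For a 0.4 SD shift at 107 per arm, power falls from about 83% to between 33% and 52% at control rates of 10% to 25%.

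These sizes rest on assumed normality, an assumed shift and assumed positive rates. The direction of the loss is the same throughout the range examined. The primary outcome is unaffected, and no criticism of the wording used for women above the cut is made.

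**What to change.** Add one sentence to the Depression section: the EPDS total score at 36 weeks is the depression outcome compared between arms, by the methods for continuous variables in the Analyses section, and the proportion scoring 13 or more is reported alongside it in each arm.

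Preferably, adjust the comparison for the baseline EPDS score, which is already collected. The t-test and Mann-Whitney test do not do this, so a regression of the 36-week score on arm and baseline score would have to be named.

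The cost is a sentence of wording and no new data. The downside is that the headline depression result becomes a difference in score, which some clinical readers find harder to interpret than a rate. Reporting the rate beside it meets most of that. If an analysis plan already specifies the score comparison, the article only needs to say so.

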##### Body Attitudes Questionnaire

Two subscales of the Body Attitudes Questionnaire [39] which relate to pregnant women will be used to assess Body Image: Attractiveness and Salience of Weight and Shape. Responses range from *definitely disagree *to *definitely agree *for each of the 10 items; higher scores indicate greater amounts of each construct.

##### Pregnancy Figure Rating Scale

The Pregnancy Figure Rating Scale was developed to evaluate body dissatisfaction amongst pregnant women [40] and provides ratings of three body parts: bust, stomach and buttocks along a scale from 1 to 10 represented by figures increasing in size for each respective body part. Women rate the figures according to their *current *and *ideal *size for each body part. Body dissatisfaction is assessed using the discrepancy between current and ideal ratings for each body part [40].

Socio-demographic data such as age, ethnicity, education level and socio-economic status will be obtained in the first questionnaire completed at recruitment.

### Power, sample size and retention

A difference between groups of 20% is deemed clinically significant. The proportion of obese women gaining weight in excess of evidence based guidelines is approximately 65% [23]. It is estimated that 107 women per study arm (total of 214 participants) is required in order to detect a difference of 20% between groups with 80% power at a 0.05 level of significance [41]. Based on current booking numbers and the prevalence of obesity at the recruitment sites, approximately 74 women will be eligible to participate each month. To accommodate an anticipated 77% participation rate [42] and a 15% attrition rate [42], the required sample will be recruited in four and a half months.

### Data Collection

Two questionnaires, one completed at recruitment and the second posted at 36 weeks will provide the self reported measures and socio-demographic data. An audit of medical records will collect data on weight gain, standards of care, number of clinicians providing care, medical complications and obstetric details.

### Ethics

The study has been approved by the Human Research Ethics Committees of Eastern Health, Barwon Health and Goulburn Valley Health, Victoria Australia and endorsed by Deakin University.

### Analyses

Analyses will be undertaken using STATA [43] and comparability of baseline characteristics will be assessed for participants in both groups. The intervention group will be compared to the control group by intention to treat analysis. Proportions of women restricting weight gain to recommended levels will be compared using chi-square tests and odds ratios. Comparison of means will be undertaken for continuous variables using t-tests where data are normally distributed, otherwise medians will be compared using Mann-Whitney U tests. Ranked or Likert scales will be analysed using cumulative odds ratios and 95% confidence intervals will be reported. Where differences in baseline characteristics exist that may be associated with outcomes, additional multivariate analysis will be performed.

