### Participants

The participants will be 214 primigravid women who attend one of the recruiting maternity services for pregnancy care (Eastern Health, Barwon Health and Goulburn Valley Health) during the recruitment period and at booking have a BMI≥30 and are less than 17 weeks gestation [8]. Women will be excluded from participating in the study if they: Are unable to give informed consent in English; have a multiple pregnancy; are currently experiencing vaginal bleeding; have a severe medical condition that prevents them from being randomised to a continuity of midwifery care model or have already commenced in a shared-care model of care with their General Practitioner.

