### Randomisation Procedure

Block randomisation will be undertaken using a computer generated randomisation sequence for each recruitment site. Following the recruitment of each woman, an opaque envelope will be selected in sequential order by the attending clinician and the contents will indicate allocation to the intervention group or the control group.

Women in the intervention group will receive 'continuity of care' defined as seeing the same midwife or small team of midwives for pregnancy care visits.

Women in the control group will receive usual clinical care. This may involve a care in one of any number of models of care available at the maternity service. Within these models of care, women see a variety of clinicians and are likely to see the same midwife at pregnancy care consultations only by chance.

All participants will receive an evidence based informational leaflet developed by the Nutrition and Dietetics Department at Goulburn Valley Health (Additional file 2). This will be modified at other sites to badge the relevant health service logo.

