### Primary outcome and measures

#### Gestational weight gain

The primary outcome is the proportion of women with a gestational weight gain within IOM guidelines. A medical record review will compare the last weight recorded in pregnancy (taken at the maternity service at 36 weeks onwards and as close as practical to birth) with the woman's booking-in weight (taken at the maternity service when the woman's BMI is calculated).

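### Randomisation is blocked by site, but the primary comparison is an unstratified chi-square reported as an odds ratio, with no confidence interval planned for the absolute difference on which the trial is sized

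*Protocol article*

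**What the plan says.** All references are to the protocol article.

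- **Design** (Randomisation Procedure): "Block randomisation will be undertaken using a computer generated randomisation sequence for each recruitment site". The sites, listed under Participants, are "Eastern Health, Barwon Health and Goulburn Valley Health", so allocation is stratified by site with three strata.
- **Primary outcome** (Gestational weight gain): "The primary outcome is the proportion of women with a gestational weight gain within IOM guidelines". This is a binary outcome.
- **Primary comparison** (Analyses): "Proportions of women restricting weight gain to recommended levels will be compared using chi-square tests and odds ratios". Neither site nor a risk difference is mentioned.
- **Adjustment** (Analyses): "Where differences in baseline characteristics exist that may be associated with outcomes, additional multivariate analysis will be performed". This is additional and conditional, and site is not named.
- **Target effect** (Power, sample size and retention): "A difference between groups of 20% is deemed clinically significant". The reference rate is 65% exceeding the guideline, and the size is given as "107 women per study arm (total of 214 participants) is required in order to detect a difference of 20% between groups with 80% power".

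**The concern.** There are two separate issues.

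**The test.** Blocking within site balances the arms across three services. If those services differ in how many women stay within the guideline, a crude comparison counts the between-site variation as error although the design has removed it from the treatment contrast. The standard error is then somewhat too large. The conditional adjustment clause is unlikely to correct this: it responds to observed imbalance, and site is the one factor that the allocation keeps balanced.

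**The effect measure.** The trial declares an absolute difference to be clinically significant, and then names only an odds ratio. An odds ratio cannot be judged against a 20-point threshold without the base rate, and its interval does not show which absolute differences the data support or exclude. The Discussion says that the results will inform a larger trial, and that use needs an interval on the absolute scale.

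**Working it through.** **1. Is the 20% absolute, and which test does the sample size assume?**

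Inputs from Power, sample size and retention: 65% against 45%, 80% power, level 0.05. Two-sided testing is assumed, because the article does not state sidedness.

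- Uncorrected: n = [1.96·√(2·0.55·0.45) + 0.842·√(0.65·0.35 + 0.45·0.55)]² / 0.20² ≈ 96 per arm.
- Continuity-corrected: n' = (n/4)·[1 + √(1 + 4/(n·0.20))]² ≈ 106 per arm, against 107 stated.
- A relative 20% (65% against 52%) would need 225, or 240 with the correction.

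The effect is therefore absolute, and the stated size comes from an ordinary unstratified two-proportion calculation. The planned chi-square is the same kind of test. Without continuity correction its power at 107 per arm is 84.2%.

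**2. Conservatism of the crude test, closed form**

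Let r be the mean within-site variance p(1−p) divided by the pooled variance. The true size of a nominal 5% crude test is about 2·[1 − Φ(1.96/√r)], and its interval is too wide by the factor 1/√r. The documents give no site rates, so the spreads below are assumptions, with equal-sized sites.

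| Exceedance rate by site | r | True size | Excess width |
|---|---|---|---|
| 63/68/74% | 0.991 | 4.9% | 0.5% |
| 50/65/80% | 0.2125/0.2275 = 0.934 | 4.3% | 3.5% |
| 45/65/85% | 0.883 | 3.7% | 6.4% |

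The first row borrows the 63 to 74% range that the Background reports across seven studies. It is only a rough proxy for variation between sites.

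**3. Crude test against Cochran-Mantel-Haenszel (CMH), simulation**

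There were 100,000 simulated trials per scenario. Assumptions, none from the documents: 214 women analysed, site shares 50/30/20%, overall control rate within the guideline 35%, and a gain of 20 points at every site.

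| Control rate by site | Type I error, crude / CMH | Power, crude / CMH | Power loss (points) |
|---|---|---|---|
| 35/35/35% | 5.2 / 5.1% | 83.4 / 83.5% | 0.1 |
| 40/30/30% | 5.1 / 5.2% | 83.6 / 83.9% | 0.3 |
| 45/30/17.5% | 4.6 / 5.0% | 83.9 / 85.8% | 1.9 |
| 55/20/7.5% | 3.1 / 5.0% | 85.6 / 90.2% | 4.6 |

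Stratifying costs nothing when sites are alike and recovers some power when they differ. The crude test shows no material inflation of type I error in any scenario.

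**4. Effect scale**

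The planned event is weight gain within the guideline. The complement of 65% exceedance is 35%. That is an upper limit for the within-guideline rate, because gains below 5 kg are also outside the range; lower bases are therefore relevant.

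- From 35%: (0.55/0.45)/(0.35/0.65) = 2.27.
- From 20%: (0.40/0.60)/(0.20/0.80) = 2.67.
- From 50%: (0.70/0.30)/(0.50/0.50) = 2.33.

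Conversely, an odds ratio of 2.27 from a 20% base is a gain of only 16.2 points.

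If 35% and 55% were observed with 107 per arm, the standard error of the difference would be √[(0.35·0.65 + 0.55·0.45)/107] = 0.0666. The risk difference is then 20 points (95% interval 6.9 to 33.1). The odds ratio is 2.27 (1.31 to 3.94). The plan as written delivers the second interval and not the first.

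**The case against.** The strongest case for leaving the plan alone has four parts.

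- **Scope.** This is a journal article. Adjustment for the stratification factor and a risk difference alongside the odds ratio are details often left to an analysis plan, which is not shown and may contain them. That limits the weight of the point. It does not remove it, because the article names a specific primary method rather than staying silent.
- **Validity and sizing.** A reader might infer that the crude test is invalid for this design, or that it does not match the sample size. The documents support neither. The chi-square compares the same two proportions on which the trial was sized, and any error from ignoring site is conservative.
- **Size.** The conservatism needs site differences that the documents do not report. With the Background's 63 to 74% range as a proxy, it is negligible. Even with the wide assumed spreads, 3.5 to 6.4% of a 13.1-point half-width is 0.035 × 13.1 = 0.46 to 0.064 × 13.1 = 0.84 points. This stands.
- **Readability.** A reader might infer that the result cannot be compared with the 20-point threshold at all. That goes too far: the two proportions can be subtracted. What is missing is the interval. A reader might also set the odds ratio of 2.27 against a risk ratio of 0.65/0.45 = 1.44, but that ratio is for exceeding the guideline. For the planned event it is 0.55/0.35 = 1.57.

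**Conclusion.** The point holds as a moderate improvement to a stated method, not as a defect of validity. The primary comparison leaves out the factor by which women are randomised, and the conditional adjustment clause is unlikely to bring it in. The cost is some conservatism and lost efficiency if site predicts weight gain: type I error of about 3 to 5%, and a power loss usually of 0 to 2 points and about 5 in the extreme scenario. If sites are similar, the effect is negligible. These figures rest on assumed site rates and shares, and on 214 women analysed.

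The effect-measure issue needs no assumption about sites. The declared threshold is absolute, the only named measure is an odds ratio, and no interval for the difference is planned. The sample size is not affected by either issue.

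**What to change.** In Analyses, or in the analysis plan before any comparison by arm, specify:

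- as the primary test, a Cochran-Mantel-Haenszel test stratified by recruitment site;
- as the primary effect measure, the Mantel-Haenszel risk difference in the proportion within the guideline, with its 95% confidence interval, to be read against the 20-point threshold;
- the odds ratio with its interval as a supplementary measure.

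Logistic regression with site as a fixed effect and a marginal risk difference is an acceptable alternative, but one of the two should be fixed in advance. Site should enter unconditionally, outside the clause on baseline differences.

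The cost is a change of wording. Site is known for every woman, so no new data are needed, and the stratified test does not call for a larger sample.

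### Continuous secondary scores: the main comparison leaves out a baseline score already collected, and observed normality decides whether means or ranks are compared

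*Protocol article*

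**What the plan says.** The Analyses section of the protocol article gives a rule for each type of outcome.

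- Continuous variables are to be compared by "t-tests where data are normally distributed, otherwise medians will be compared using Mann-Whitney U tests".
- For ordered responses: "Ranked or Likert scales will be analysed using cumulative odds ratios and 95% confidence intervals will be reported".
- Baseline comparability will be assessed, and "Where differences in baseline characteristics exist that may be associated with outcomes, additional multivariate analysis will be performed".

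Under Psychological factors during pregnancy, readiness to change, anxiety, depression and body image "will be assessed at baseline and at 36 weeks gestation". Data Collection has the first questionnaire completed at recruitment. Randomisation Procedure has the allocation envelope taken after recruitment, so the baseline scores appear to precede allocation.

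The article does not say which psychological scales count as continuous and which as ranked or Likert. Nor does it say whether the t-test is applied to the 36-week score or to the change from baseline. Power, sample size and retention covers the primary outcome only: "107 women per study arm (total of 214 participants) is required".

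**The concern.** Three features of the rule for continuous variables deserve attention.

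1. **Baseline is not part of the main comparison.** The strongest predictor of a woman's 36-week score is usually her own earlier score, and it is already being collected. The article uses it only in an additional analysis, and only if the arms are seen to differ. The gain in precision from adjustment does not depend on imbalance, so a trigger based on imbalance misses most of it. It also makes the choice of analysis depend on the data.
2. **Observed normality picks the test.** A t-test targets a difference in means. Mann-Whitney targets a rank-based quantity: the probability that a woman in one arm scores higher than a woman in the other. Under the rule, the quantity being estimated is not known until the data are seen, and it may differ from scale to scale. At about 100 women per arm, a comparison of means does not need normal data.
3. **Mann-Whitney is said to compare medians.** That holds only if the two distributions have the same shape and differ by a shift.

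At stake are the precision and interpretability of secondary outcomes for which the article states no power.

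**Working it through.** **Inputs from the article.** 107 per arm; 65% of women exceeding the weight-gain guideline; a 20-point difference; 80% power; significance level 0.05, taken as two-sided; 15% attrition. **Assumed.** The baseline to 36-week correlation r is not in the article, so a range of 0.3 to 0.7 is shown.

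**Step 1: the article's own figure.** For 65% against 45%, the mean proportion is 0.55. Without continuity correction:

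n = [1.96 × √(2 × 0.55 × 0.45) + 0.842 × √(0.65 × 0.35 + 0.45 × 0.55)]² / 0.20² = 96 per arm.

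With continuity correction: n = (96/4) × [1 + √(1 + 4/(96 × 0.20))]² = 106 per arm. This agrees with the stated 107 to within rounding. The 107 is therefore a figure for the primary binary outcome and says nothing about the scales.

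**Step 2: precision given up.** Linear adjustment for baseline multiplies the variance by 1 − r². The standardised difference detectable with 80% power is (1.96 + 0.842) × √(2(1 − r²)/n). For n = 107 and no adjustment this is 2.80 × √(2/107) = 0.383 SD.

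| r (assumed) | 1 − r² | Variance removed | Detectable at 107 per arm | Detectable at 91 per arm |
|---|---|---|---|---|
| no adjustment | 1 | 0% | 0.383 SD | 0.415 SD |
| 0.3 | 0.91 | 9% | 0.365 SD | 0.396 SD |
| 0.5 | 0.75 | 25% | 0.332 SD | 0.360 SD |
| 0.7 | 0.51 | 49% | 0.274 SD | 0.297 SD |

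At 107 per arm, power for an assumed difference of 0.4 SD rises from 83% to 87%, 92% and 98% for r = 0.3, 0.5 and 0.7. In terms of sample size, 1/(1 − r²) is 1.10, 1.33 and 1.96, that is, worth 10%, 33% and 96% more women.

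The 91 column is 107 × 0.85, in case attrition comes out of the 107. The recruitment arithmetic, 74 × 0.77 × 4.5 × 0.85 = 218, suggests instead that 214 is already net of attrition, so the 107 column is the main one.

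**Step 3: the normality switch.** Simulation, 10,000 runs, 91 per arm. The t-test was used if Shapiro-Wilk did not reject at 5% in either arm, and Mann-Whitney otherwise.

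- Normal data, no difference: the rule moved to Mann-Whitney in 9.7% of runs (two 5% tests give 1 − 0.95² = 9.75%). Type I error 4.8%.
- Skewed data (gamma, shape 4), no difference: the rule moved in 99.6% of runs. Type I error 5.0%.

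The switch changes what is estimated. It did not inflate type I error in either setting.

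**Step 4: medians.** One arm was exponential with its median moved to zero, the other its mirror image, so both medians are 0 and the skews are opposite. Mann-Whitney rejected in 62% of runs. The example is deliberately extreme, but it shows that the test is not in general a test of medians.

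**The case against.** The case on the other side has several parts.

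- **Baseline is not ignored.** A reader might infer that the plan throws the baseline away and that chance imbalance passes unchecked into the 36-week comparison. The article does not support that: it assesses baseline comparability and provides an additional multivariate analysis where differences exist. What remains is that this adjustment is conditional and supplementary.
- **Not every scale need follow this route.** A reader might infer that all the psychological scales go to a t-test or Mann-Whitney. The article does not say so. Readiness to change has five-point agreement items ("There are 12 items which are rated on a five point scale from Strongly agree to Strongly disagree"), the anxiety and body-attitude responses are also ordered categories, and such scales may fall under the cumulative-odds rule. Depression also has a cut-off. The objection stands, and the point is limited to scores analysed as continuous. The cumulative-odds rule names no baseline adjustment either.
- **Change scores are not excluded.** True. A change score has relative variance 2(1 − r): 1.4, 1.0 and 0.6 for r = 0.3, 0.5 and 0.7. Each exceeds the matching 1 − r², so baseline adjustment is better in either case.
- **Model detail belongs in the analysis plan.** Neither the full protocol nor an analysis plan is shown, and a missing model specification would be no finding. The point rests on what the article does state: the main test, the data-driven choice between tests, the conditional role of baseline, and an incorrect description of Mann-Whitney.
- **Mann-Whitney can yield an interpretable estimate.** A Hodges-Lehmann shift with an interval could accompany it, and the article does not rule that out. It would be too strong to say that no interpretable result is possible.
- **The depression cut-off.** A reader might take "Women will be classified as probably clinically depressed using a cut-off score of ≥ 13" to mean that the score itself will not be analysed. The article does not say that, and no stated error needs correcting there.

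**Conclusion.** The point holds as an improvement to the secondary analyses. For continuous scores measured twice, the main comparison is unadjusted, baseline adjustment waits on observed imbalance, the data choose between a mean difference and a rank-based quantity, and Mann-Whitney is wrongly described as comparing medians in general.

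The size depends on a correlation that the article does not give. For r between 0.3 and 0.7, the forgone reduction in residual variance is 9% to 49%, and the detectable difference at 107 per arm could be 0.365 to 0.274 SD instead of 0.383 SD. At r = 0.3 the gain is small. The figures apply to a linear model for a continuous score with the baseline taken before allocation, and compare it with a test of the 36-week score alone. They do not carry over to the cumulative-odds analyses.

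A reader might go further and infer bias or false positives. Neither is supported: randomisation keeps the unadjusted comparison unbiased, and the test switch held its nominal level in both settings simulated. The primary outcome, its chi-square and odds-ratio analysis, and its sample size are untouched.

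**What to change.** 1. For each scale score measured at baseline and 36 weeks and analysed as continuous, prespecify as the main analysis a linear regression of the 36-week score on arm, baseline score and site. Site belongs in the model because a separate randomisation sequence is generated for each one. Report the adjusted mean difference with its 95% CI, using robust or bootstrap standard errors if the scores are skewed.
2. For any twice-measured scale analysed by cumulative odds ratios, include the baseline score as a covariate in that model, and label the result as an odds ratio conditional on baseline.
3. State which scales fall under each rule.
4. Remove the switch based on normality and the statement that Mann-Whitney compares medians.

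The cost is wording only, settled before the data are analysed. The baseline scores are already being collected, and no additional women, visits or questionnaires are needed.
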